Further analyses will examine the effects of the CBT + Yoga intervention on potential mediators of smoking behavior change, and the relationships of the potential mediators to smoking cessation. The potential mediators of interest include changes in affect, perceived stress, well being, and self-efficacy as well as cigarette craving and withdrawal symptoms. We will also examine for any differences in the effects of the CBT + Yoga intervention versus the CBT + Wellness intervention on these intermediate variables. Given the limited sample size in the proposed study, these analyses will be exploratory in nature, and within the context of these analyses, we will be trying to establish 2 of the 3 key directional effects needed to describe potential mediators as noted by Baron and Kenny [52], that is we will be investigating which of the potential mediating variables are affected by the treatment, and which of these potential mediators are also related to the key smoking cessation outcome variables. The strongest evidence for mediation is time-ordered, and these analyses will examine the effects of treatment on each of the various potential mediating variables at immediate post-treatment (8 week assessment), and include analyses of possible longitudinal treatment effects extending to the 3 and 6 month follow up. These analyses will consist of a series of repeated measures analyses of covariance using the baseline measure of each potential mediator variable as a covariate and 3 repeated measurements (end of treatment, 3 and 6 month follow up). We will conduct these analyses using Proc MIXED in SAS, which will allow us to easily conduct contrast tests to compare both between and within group effects across time. Proc MIXED also accommodates missing values under the assumption of missing at random [53], and will allow us to make maximum use of the existing data to detect treatment effects. To examine the effects of potential mediator variables on treatment outcome we will conduct a series of time-ordered logistic regressions, (e.g., post-treatment value of smoking self-efficacy, perceived stress and well-being, etc. predicting both continuous abstinence and 7-day point prevalence at 3-month follow-up).

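### The only predictor named for the mediator-to-abstinence regressions is the week-8 score, so a variable that yoga shifts could be called a mediator because of its pre-treatment level

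*Protocol article*

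**What the plan says.** All of this stands in the Protocol article, Planned Analyses.

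- Mediators: "The potential mediators of interest include changes in affect, perceived stress, well being, and self-efficacy as well as cigarette craving and withdrawal symptoms".
- Aim: "we will be trying to establish 2 of the 3 key directional effects needed to describe potential mediators". The two are that treatment affects the variable and that the variable is related to cessation.
- Arm to mediator: repeated measures analyses of covariance, "using the baseline measure of each potential mediator variable as a covariate and 3 repeated measurements".
- Mediator to abstinence: "To examine the effects of potential mediator variables on treatment outcome we will conduct a series of time-ordered logistic regressions". The example in brackets has the "post-treatment value of smoking self-efficacy, perceived stress and well-being, etc. predicting both continuous abstinence and 7-day point prevalence at 3-month follow-up". No covariates are listed.
- Status: "Given the limited sample size in the proposed study, these analyses will be exploratory in nature".

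**The concern.** Within one section the mediator is first a change, then a baseline-adjusted outcome, and finally a level at week 8. That level mixes where a woman started with how far she moved. A woman who was confident before treatment is likely to be confident at week 8 and may also be more likely to quit. The week-8 score can therefore predict abstinence at 3 months even if the movement during treatment had no bearing on it.

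This matters most for the variables the trial is built around, those that yoga is expected to move (the Background cites stress and negative affect). They should pass the first step. The second step is then the only check that separates a change that helped a woman quit from a better starting position, and an unadjusted level cannot make that separation. The Discussion looks to this work for insight into how yoga may act.

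**Working it through.** The article gives no figure for these regressions. Its 60% power statement (Sample size) is about estimating the treatment effect and is not used here.

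**Inputs from the article:** 60 participants; step 1 adjusted for baseline; step 2 using the week-8 value.

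**Assumptions:** 30 per arm; two-sided 5% tests; step 1 simplified to a week-8 analysis of covariance; and the correlations, odds ratios, abstinence rates and shift given below.

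**Model.** With standardised baseline M0, arm A (0/1) and independent noise e:

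- M8 = r·M0 + √(1−r²)·e + d·A
- logit P(abstinent) = a + β·M0, so the change has no effect on quitting.

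**Step 2 with the raw score.** To a linear approximation the slope on M8 is β·cov(M0, M8)/var(M8) = β·r/(1 + d²/4). With d = 0.5 the denominator is 1.0625.

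- Weak end (odds ratio 1.5, r = 0.5): 0.405 × 0.5/1.0625 = 0.19, an apparent odds ratio of about 1.21.
- Strong end (odds ratio 2.5, r = 0.7): 0.916 × 0.7/1.0625 = 0.60, an apparent odds ratio of about 1.83.

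With M0 and A in the model, what remains of M8 is e, which is unrelated to quitting. The slope is then zero.

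**Both steps together, yoga shifts the variable by 0.5 SD.** Simulation with β = 0.8 per SD, intercept set at 25% abstinent, 1,000 trials per row:

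| r | Step 1 passes | Step 2 passes, raw | Product | Both, simulated | Both, with baseline and arm |
|---|---|---|---|---|---|
| 0.4 | 53.8% | 15.1% | 8.1% | 8.0% | 2.9% |
| 0.6 | 64.4% | 28.0% | 18.0% | 18.0% | 2.7% |
| 0.8 | 87.8% | 46.5% | 40.8% | 39.4% | 4.1% |

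Over a more moderate grid (odds ratio 1.5-2.5, r 0.5-0.7, 15% or 25% abstinent, same shift), step 2 alone gives a false link in 6-41% of trials, against 4-5% adjusted. Both steps are passed in about 3-31%, against 2-4% adjusted.

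**Both steps, yoga does not shift the variable.** Step 1 then passes about 5% of the time, which caps the joint rate: 0.4-4.9% per candidate with the raw score and 0-1.4% adjusted.

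**Change score instead.** Within arm, cov(M0, M8−M0) = r−1 and var(M8−M0) = 2(1−r), so the slope is −β/2 whatever r is. A false link remains, with its sign reversed. The simulated false-link rate with change score plus arm is 8-39% when yoga does not move the variable.

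**The case against.** **The covariates may simply be unstated.** The regression appears as an example in a condensed article, and covariate lists are commonly left to the analysis plan. This stands in part: the text does not say that baseline and arm are left out. But the form of the predictor is stated. It is a level, and it does not match the definition of the mediators given in the same section.

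**A reader might infer that stable pre-treatment traits will be reported as mechanisms of yoga.** The document does not support that. A candidate must also be affected by treatment in a randomised, baseline-adjusted comparison, which holds a trait that yoga does not move to at most about 5%. The step 2 rate alone overstates the risk.

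**Not fitting arm with the mediator is a declared limit.** This stands. The section says that it seeks only two of three effects and gives sample size as the reason. The cost is also small: 7-9% false links against about 4%, and that when yoga shifts the mediator by 0.8 SD and triples the odds by another route.

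**Adjustment can lose power.** This stands. If the change drives quitting (odds ratio 2 per SD), adding baseline raises power from 27% to 40% at 15% abstinent and from 36% to 55% at 25%. If the week-8 level itself drives quitting, which is also plausible for self-efficacy, power falls from about 40-59% to 22-45%.

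**The repair is partial.** This stands. If a latent trait drives quitting and is measured with error at both visits, false links fall from 18-91% to 6-26%, not to 5%. In those settings a change score plus arm stays at about 3-6%, but it fails when the baseline level itself is the driver, so it cannot be relied on.

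**The exploratory label** is tied to the small sample. It tempers the claims but does not remove a bias.

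**Conclusion.** The point holds in a narrow form. The regressions are described with a predictor that does not match the stated definition of a mediator. As described, they can let a variable that yoga shifts be named a potential mediator because of where women started. The size is about 3-31% of trials against 2-4% with adjustment. It rests wholly on assumed values, since the article gives no correlation, prognostic strength or abstinence rate for these scores. At the weak end (odds ratio 1.5, correlation 0.5) the problem is slight; with a strongly prognostic baseline it is large.

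The article does not show that baseline and arm will be omitted, nor that unmoved traits would be presented as mechanisms. No primary or secondary treatment comparison is touched. Whether the week-8 score itself follows quitting during treatment is a separate question, which this adjustment does not settle.

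**What to change.** State that, for each mediator with a baseline score, 3-month abstinence is regressed on the week-8 value adjusted for that mediator's baseline value and for arm. Report the mediator odds ratio with its interval, and the arm odds ratio with and without the mediator. Do not use a simple change score instead.

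Prefer Firth's penalised likelihood. At 15-25% abstinent, 60 × 0.15 = 9 to 60 × 0.25 = 15 women would be abstinent, which is 3-5 per predictor with three predictors. In simulation with 1-3 predictors and 10-25% abstinent, maximum-likelihood log odds ratios averaged 1.06-1.22 times the truth, and Firth's 0.98-1.03 times.

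Table 1 marks a baseline for self-efficacy and withdrawal, so the fix applies to them. It also applies to well-being if that is scored from the SF-36, which the Measures section lists among the assessments. PANAS is marked only for weeks 1-8, and Measures names no perceived-stress scale. For any mediator without a baseline score, report the result as an association and not as evidence of mediation.

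The cost is a change of wording and two extra parameters per exploratory model, with no new assessments. The statistical price is the possible loss of power and the incomplete removal of bias described above; both should be acknowledged when results are reported.

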### Analyses of Baseline Data

The baseline demographic, psychosocial, and smoking-related characteristics of the study participants are described here using means, standard deviations, range values and proportions. Stage of Change for Smoking Cessation is calculated in two ways, with the first based solely on intention to quit, while the second classifies participants into the Preparation stage if they both intend to quit in the next 30 days and they have made at least 1 quit attempt (≥24 hr) in the past year. To describe participant's experience with withdrawal symptoms during previous quit attempts we calculated the percentage of the sample that endorsed 3 or higher on the Withdrawal Symptoms checklist [37] (scored from 1 = "not at all' to 5 = "extremely"), which assessed the severity of nicotine withdrawal symptoms.

## Discussion

If shown to be effective, yoga can offer an alternative to traditional exercise for reducing negative symptoms that often accompany smoking cessation and predict relapse to smoking among recent quitters. Yoga may enhance the effects of CBT by providing an alternate method for coping with stress and cigarette cravings, and may be associated with improvements in mood and quality of life. Yoga is intended to be a lifelong practice that can potentially reinforce quitting smoking once formal smoking treatment ends.

In addition to making quitting smoking uncomfortable, symptoms including perceived stress, negative affect and the overall severity of withdrawal symptoms have all been shown to increase the individual's risk for relapse to smoking. Relapse to smoking within the first week of quitting is preceded by increases in withdrawal symptoms, including craving for cigarettes, distress, and reductions in positive affect [54]. Perceived stress and negative affect have also been shown to predict time to relapse among recent ex-smokers [5,6,55,56]. Providing smokers with methods of coping with stress should improve their ability to quit and remain quit [57].

Several studies have documented that traditional (western) aerobic exercise improves smoking cessation among women [12,22,58]. Vinyasa yoga, which includes both aerobic exercise as well as other features such as focused attention and deliberate regulation of breathing, may be especially beneficial to women who are trying to quit smoking. The goal of this study is to examine the utility of a program of yoga as a complementary treatment to cognitive-behavioral therapy for smoking cessation.

This study is an initial investigation of the efficacy of yoga as a complementary treatment for smoking cessation among women. While our prior studies used a 12-week treatment protocol to ensure that changes in physical fitness could be measured, we chose to deliver treatment over 8 weeks. This choice was made for several reasons. First, the effects of exercise on mood and cigarette craving seen in our previous study [21] were acute, rather than chronic-training effects. Thus, it seems likely that the effects of yoga practice on these symptoms would also be produced acutely. The 12-week protocol used in our other studies was chosen to allow sufficient time for fitness changes to take place. Since we were not hypothesizing that fitness changes were responsible for the effect of yoga on smoking cessation, measuring a training effect was deemed unnecessary. Second, the use of a shorter overall treatment program reduces subject burden and is likely to lower the risk of dropout. Third, participants in our previous studies were very unlikely to make an initial quit after week 8, therefore extending CBT beyond week 8 seemed unlikely to increase treatment effectiveness. Another design choice made in developing this study was the use of a Health & Wellness program as a comparison condition. An alternative design would have been to test CBT alone (with no adjunctive program) compared to CBT plus yoga. In some ways, the second option would have provided a more "real world" comparison, in that the use of yoga with CBT does add additional time and treatment burden to quitting smoking. However, we chose to use the Healthy & Wellness program to control for the amount of time participants were in contact with the research staff (contact-control) and to equalize subject burden. Last, because this is an initial study of the potential for using yoga as a complementary therapy in smoking cessation, we also chose to use a variety of measures of affect, self-perception and experiential variables (e.g., FMI assessment of mindfulness). The design chosen for this study will allow us to explore potential mediators of intervention efficacy so that we may better understand the mechanism(s) by which yoga may act as an effective complementary treatment for smoking cessation.

Innovative treatments are needed that address barriers to successful smoking cessation among men and women. The practice of yoga has been linked to improvements in affect, reductions in stress and anxiety, increases in self-efficacy and improvements in overall well-being in addition to producing improvements in cardiopulmonary functioning [29-32]. Therefore, yoga may prove to be a more effective complementary treatment for smoking cessation than traditional aerobic exercise.
